### Methods: Data collection, management, and analysis

#### Plans for assessment and collection of outcomes.

Evaluations will be made at baseline, at the end of the intervention period (fourth week), and at 12 weeks follow up. All evaluations will be performed digitally through a questionnaire where participants will be invited to self-report their level of pain (PI-NRS), their functional disability (NDI), their QoL (SF-12), and to rate their adherence to exercises. At the baseline education session, questionnaires and evaluation tools will be explained to participants to resolve any doubt while answering.

#### Plans to promote participant retention and complete follow-up.

Daily notifications will be intended to promote participant retention. Participants will also be given a phone number and will be informed that they can call the principal investigator if ever a doubt or a misunderstanding with their intervention protocol occurs. This availability may help participants completing the follow-up. Moreover, participants using the smartphone app will benefit from additional methods to promote self-monitoring and self-management. The information included in the app may also help to encourage participants to complete the study.

### Data management

All participants will be assigned a study identification code linked to their personal information that will be stored in a protected database accessible only to the principal investigator (*SS* in the authors’ list).

### Statistical methods

All data will be analyzed using SPSS version 23. The Shapiro-Wilk test will evaluate the normal distribution of quantitative data. If the distribution will be normal and the variances are equal, the quantitative data will be reported as mean ± standard deviation, and 95% confidence interval. Otherwise, data will be expressed as median (interquartile range). Categorical data will be expressed in percentage frequencies. The between-group differences in the mean changes of the outcome measures (PI-NRS, NDI, SF-12, adherence) after intervention will be calculated using repeated measures mixed models with participants from the IG as random effect, and group (IG or CG) and time (baseline, four weeks, and 12 weeks) as fixed effects, and with adjustments for baseline imbalance. The Spearman rank test or Pearson product-moment correlation coefficient analysis will be used to analyze the associations between clinical data and mean changes in the outcome measures. Two-sided statistical significance is set at a p value < 0.05.

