### Outcomes

The main outcome measure is pain intensity, evaluated according to the PI-NRS [28–30]. The latter is a commonly used tool to measure a person’s pain intensity [28–30]. It is simple, quick, and widely accepted in both clinical and research settings [28–30]. Participants will be asked to indicate their current level of pain on a line from 0 (no pain) to 10 (unbearable pain) [28–30].

Secondary outcome measures are function (***i.e.,*** neck disability index (NDI)), QoL and participants’ adherence to self-exercises. The French validated version of the NDI will be used to assess the impact of NP on individual’s daily functioning [31]. The scale consists of a set of questions addressing various aspects of NP and its influence on activities such as personal care, lifting, reading, working, and recreation. Participants will be asked to rate their level of disability or limitation on a scale for each activity. The total score provides a quantitative measure of the perceived disability associated with NP, with higher scores indicating greater impairment [32]. The French validated version of the short form 12 (SF-12) will be used to measure health-related QoL. The SF-12 is a shorter version of the short form 36, which assesses an individual’s physical and mental well-being. The SF-12 is often utilized in health research, clinical practice, and population health studies [33,34]. Adherence will be measured via two methods. First, it will be evaluated using a frequency-based response scale (***i.e.,*** never, seldom, often, almost always, and always) adapted from the adherence scale of Sluijs et al. [35]. Adherence will then be treated as a dichotomous variable (***i.e.,*** adherent or not adherent), participants who will report “always” or “almost always” will be considered adherent [21]. Second, adherence will be measured based on the frequency of exercise sessions completed. Participants who engage in exercises three or more times per week will be categorized as demonstrating “full adherence” whereas those who exercise twice per week or less will be considered to exhibit “partial adherence”. These combined methods ensure a comprehensive evaluation of adherence, capturing both self-reported behavior and objective frequency of exercise.

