#### Blinding.

One of the coauthors (*AC* in the authors’ list) who is blinded to the treatment arm will analyze data. The study principal investigator, in charge of explaining and delivering interventions (*SS* in the authors’ list), and the participants will not be blinded to the group allocation.

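### The mixed model for the outcomes gives a random effect to app-group participants only; taken literally, it miscalibrates the test of the difference in mean change and conflicts with the blinded analyst

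*Protocol article*

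**What the plan says.** The Statistical methods section gives one model for all outcomes. Its target is "The between-group differences in the mean changes of the outcome measures (PI-NRS, NDI, SF-12, adherence) after intervention". These differences "will be calculated using repeated measures mixed models with participants from the IG as random effect", with "group (IG or CG) and time (baseline, four weeks, and 12 weeks) as fixed effects", and "with adjustments for baseline imbalance". The test level follows: "Two-sided statistical significance is set at a p value < 0.05". No group-by-time term, residual covariance structure or form of baseline adjustment is given.

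The Outcomes section fixes the primary variable: "The main outcome measure is pain intensity, evaluated according to the PI-NRS". The section on assessment and collection of outcomes sets the same visits for everyone, without distinction by group: "Evaluations will be made at baseline, at the end of the intervention period (fourth week), and at 12 weeks follow up". The Blinding section says that the coauthor "who is blinded to the treatment arm will analyze data".

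**The concern.** Each participant in either arm contributes up to three scores, and scores from one person are correlated. A participant random effect is the part of the model that carries this correlation. If only app-group participants have one, and nothing else in the model links a person's visits, the control group's scores are treated as independent observations.

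The residual variance is then estimated from a mixture. In the app group it reflects variation within persons; in the control group it absorbs variation between persons as well. It comes out too large for comparisons within persons, while the control group's contribution to comparisons between persons comes out too small. At stake is the calibration of the p-value and confidence interval for pain intensity, the primary outcome.

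A second consequence is practical. Whoever fits this model must be told which participants, or which coded arm, receive the random effect. That reveals the arm to the analyst who is meant to be blinded.

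**Working it through.** **Inputs from the article.** Three visits; 25 per group; two-sided level 0.05; difference in change d = 0.58; SDs of change 1.85 and 1.26. The article states no figure for this model apart from the 0.05 level. Its sample-size arithmetic reproduces: s² = (16 × 1.85² + 16 × 1.26²)/32 = 2.505; n = 2 × 2.505 × 2.8²/0.58² = 116.8, so 117; 70 × 117/187 = 43.8, so 44; 44/0.9 = 48.9, so 50 in equal arms. Whether that sample size is adequate is a separate matter.

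**Assumption.** The article gives no within-participant correlation r. I take 0.3, 0.5 and 0.7, with compound symmetry and equal variance (set to 1) at each visit.

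**What the literal model estimates (large samples).**
- App group: 2 within-person degrees of freedom per person, with variance 1 − r. The between-person mean square is estimated separately and tends to 1 + 2r.
- Control group: all 3 degrees of freedom per person go into the residual, with average variance [2(1 − r) + (1 + 2r)]/3 = 1.
- Residual variance: [2(1 − r) + 3]/5 = 1 − 0.4r. The true within-person variance is 1 − r.
- Random-intercept variance in the app group: [(1 + 2r) − (1 − 0.4r)]/3 = 0.8r.

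**Model SE divided by true SE, by contrast.**
- Difference in change, baseline to week 12 (needs a group-by-time term): √[(1 − 0.4r)/(1 − r)].
- Group effect averaged over the three visits: √[(2 + 1.6r)/(2 + 4r)].
- Simple group difference at week 12, from a model with group-by-time means: the fitted visit variances are 1 + 0.4r (app) and 1 − 0.4r (control). They sum to 2, the true value, so the ratio is 1.

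| | r = 0.3 | r = 0.5 | r = 0.7 |
|---|---|---|---|
| Change: SE ratio | √(0.88/0.70) = 1.12 | √(0.80/0.50) = 1.26 | √(0.72/0.30) = 1.55 |
| Change: simulated type I error | 0.030 | 0.015 | 0.003 |
| Average over visits: SE ratio | √(2.48/3.20) = 0.88 | √(2.80/4.00) = 0.84 | √(3.12/4.80) = 0.81 |
| Average over visits: simulated type I error | 0.083 | 0.096 | 0.116 |
| Weeks 4 and 12, baseline as covariate: simulated type I error | 0.065 | 0.068 | 0.072 |
| Week-12 difference: simulated SE ratio | 0.998 | 0.999 | 0.996 |
| Week-12 difference: simulated type I error | 0.048 | 0.048 | 0.048 |

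The simulations are REML fits with no true effect and 25 per arm. They used 20,000 trials per setting for the change and averaged contrasts, 2,500 for the baseline-adjusted one and 40,000 for week 12. With 2,500 trials the Monte Carlo standard error is about √(0.07 × 0.93/2500) = 0.005. The baseline-adjusted inflation is smaller partly because, given baseline, the correlation between the two later visits is (r − r²)/(1 − r²) = r/(1 + r), that is 0.23, 0.33 and 0.41. With 22 per arm, the results for the change and averaged contrasts are nearly the same.

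**Power for the difference in change.** The true SE at 25 per arm is √(2 × 2.505/25) = 0.448, and 0.58/0.448 = 1.30. A correctly calibrated test has power of about 25%. The literal model must exceed 1.96 × 1.12, 1.96 × 1.26 or 1.96 × 1.55 true standard errors, which leaves about 18%, 12% and 4%.

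**After correction.** With a random intercept for every participant, simulated type I error is 0.048–0.052 for the change, 0.047–0.051 for the averaged effect and 0.046–0.050 for the baseline-adjusted effect.

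**The case against.** The strongest reply is that the phrase is a slip for participants in general. The conflict with the blinded analyst supports this, since the authors are unlikely to have intended a model that their own analyst could not fit blind. If the software run uses every participant's identifier, the problem disappears. Likewise, calling the model a repeated-measures one is compatible with a within-participant residual covariance in both arms, which would largely remove it, and an article may leave that structure to the analysis plan. All of this is plausible. It does not remove the point: this is not an omission but an explicit statement, it is wrong as it stands, and nothing else in the article corrects it.

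A reader might infer more: that every between-group comparison is invalid, or that false positives are simply inflated. The article does not support either reading. The simple week-12 difference remains calibrated. For the difference in change, which the article names as its target, the test is conservative: it costs power and does not create false positives. Inflation arises for a group effect averaged over visits, which is not a difference in change, and mildly for the baseline-adjusted effect. Because no group-by-time term is listed, the article does not settle which contrast will be tested.

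Nor is the blinding conflict a separate defect. It comes from the same words and goes with the same edit.

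**Conclusion.** The point stands as an error in the stated model. The consequence depends on the contrast: loss of power for the article's own target, type I error of up to about 12% for an effect averaged over visits, a small excess with baseline as covariate, and none for a plain week-12 comparison. These sizes rest on correlations of 0.3 to 0.7, which are my assumption, on compound symmetry, and on no residual covariance being added. The error vanishes only at zero correlation. As the sentence governs the test of the primary outcome, it should be corrected before analysis.

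**What to change.** In Statistical methods, replace the random-effect phrase with *participant (both groups) as random effect*, or state a within-participant covariance over the three visits that is common to both arms. In the same sentence, add the group-by-time term and name its contrast, the between-group difference in change, as the test of the primary outcome. The analyst can then fit the model with arms coded A and B, without being told which is the app group. The cost is one sentence; no data collection, sample size or budget is affected.

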### Sample size

The null hypothesis [36] was H_0_: m_1_ = m_2_, and the alternative hypothesis was H_a_: m_1_ = m_2_ + d, where “***d***” is the difference between two means and n_1_ and n_2_ are the sample sizes for the interventional and control groups, such N = n_1 _+ n_2_. The sample size was estimated using the following predictive equation [36]: $\text{n}\;=\;[\text{2}\;{\text{s}}^{\text{2}}\;{\left({\text{Z}}_{\text{1}-\alpha /\text{2}}\;+\;{\text{Z}}_{\text{1}-\beta }\right)}^{\text{2}}]/{\text{d}}^{\text{2}}$, where

“***n***” is the number of participants;“***Z***_***1-α/2***_” is the normal deviate at a level of significance (type I error at 2-sided = 1.96 at 5% level of significance);“***Z***_***1-β***_” is the normal deviate at 1-β% power with β% of type II error (0.84 at 80% statistical power);“***d***” is the expected difference between average changes of PI-NRS from two groups; and“***s***” is the common variance (standard deviation) of PI-NRS means of two groups. “***s***” was calculated according to the following formula [36]: ${\text{s}}^{\text{2}}\;=\;[({\text{n}}_{\text{1}}-\text{1x}\;{{\text{s}}_{\text{1}}}^{\text{2}}\;+\;({\text{n}}_{\text{2}}-\text{1})\;\text{x}\;{{\text{s}}_{\text{2}}}^{\text{2}}]/({\text{n}}_{\text{1}}+{\text{n}}_{\text{2}}-\text{2})$ .

“***d***” and “***s***” values were obtained from a previous South Korean study [37] including 34 patients (17 in the IG and 17 in the CG). The patients in the IG performed exercises using a video-based app system, whereas those in the CG performed exercises using an image- and text- based printout [37]. In-home training was implemented for six weeks in both groups [37]. The NP intensity was measured before and after the intervention via the PI-NRS. Kim and Shin [37] reported that within both groups, the PI-NRS improved significantly after the intervention. At the end of the intervention, PI-NRS’ changes (expressed as means ± standard deviation) for the IG and CG were 2.23 ± 1.85 and 1.65 ± 1.26, respectively (“***d***” is therefore equal to 0.58 (0.58 = 2.23 - 1.65). Based on the aforementioned study [37], where n_1_ = 17, n_2_ = 17, s_1_ = 1.85, s_2_ = 1.26, “***s***^***2***^” is equal to 2.51 [2.51= [(17-1) x 1.85^2^ + (17-1) x 1.26^2^]/(17 + 17-2)].

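### The model is meant to give the between-group difference in change, but its listed fixed effects include no group-by-time term, so fitted as written it understates that difference

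*Protocol article*

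**What the plan says.** One sentence of the protocol article's Statistical methods section gives both the target and the model: "The between-group differences in the mean changes of the outcome measures (PI-NRS, NDI, SF-12, adherence) after intervention will be calculated using repeated measures mixed models". The random part is given as "with participants from the IG as random effect". The fixed part is "group (IG or CG) and time (baseline, four weeks, and 12 weeks) as fixed effects, and with adjustments for baseline imbalance". Baseline is therefore an outcome row in the model as well as, possibly, something adjusted for. The section names neither an interaction nor a primary visit.

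The Sample size section plans on the same target: d "is the expected difference between average changes of PI-NRS from two groups", set at 0.58 PI-NRS points. The schedule is "Evaluations will be made at baseline, at the end of the intervention period (fourth week), and at 12 weeks follow up". The Objective section hypothesises that the app is superior both immediately and in the short term.

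**The concern.** When baseline is one of the time levels, a between-group difference in change is a group-by-time contrast. A model with group and time main effects alone forces the arm difference to be the same at baseline, week 4 and week 12, and reports that single common value. The baseline visit precedes treatment, so it pulls the estimate towards zero and also carries in any chance baseline difference.

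This is the only between-group analysis the article describes, and it covers the primary outcome. Followed literally, it would report an effect that is too small, with an interval centred in the wrong place, for a quantity other than the one used to plan the trial. It would also give no separate week-4 and week-12 effects with which to address the two hypotheses on timing.

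**Working it through.** Inputs from the Sample size section: changes of 2.23 (SD 1.85) and 1.65 (SD 1.26), 17 per arm; "type I error at 2-sided = 1.96 at 5% level of significance"; "0.84 at 80% statistical power". Three assessments per participant. The protocol gives no effect trajectory, within-person correlation or residual covariance, so these are assumed below. Improvement is counted as positive.

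**1. The plan's own figures.** d = 2.23 − 1.65 = 0.58. s² = (16 × 1.85² + 16 × 1.26²)/32 = 2.505, given as 2.51. n = 2 × 2.51 × (1.96 + 0.84)²/0.58² = 116.99, so 117. Then 70 × 117/187 = 43.8, so 44, and 44/0.9 = 48.9, taken as 50 for equal arms. The arithmetic reproduces. Whether that size is adequate is a separate question; what matters here is that d is a difference in change.

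**2. What the group coefficient estimates.** Let δ0, δ4 and δ12 be the arm differences at the three visits. With main effects only, a random intercept and complete data, the group coefficient is (δ0 + δ4 + δ12)/3. Randomisation gives E(δ0) = 0, so its expectation is (δ4 + δ12)/3, which is 2/3 of the average post-baseline effect (δ4 + δ12)/2. With 0.58 at both visits this is (0 + 0.58 + 0.58)/3 = 0.387. The result is the same whether the random intercept is given to everyone or to IG participants only.

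**3. Relative to the week-12 effect** (random intercept, δ12 = 0.58):

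| Effect over time | Coefficient ÷ δ12 | Expected estimate |
|---|---|---|
| Equal at weeks 4 and 12 | 2/3 = 0.667 | 0.387 |
| Half present at week 4 | 1.5/3 = 0.500 | 0.290 |
| Linear growth (one third at week 4) | 1.333/3 = 0.444 | 0.258 |
| Week 12 only | 1/3 = 0.333 | 0.193 |

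**4. Other covariance structures.** Generalised least squares then weights the visits unequally. With equal effects at both visits the ratio is 0.60 under AR(1) with correlation 0.5, 0.565 under AR(1) with 0.7, and 0.22 if the SD grows 1 : 1.4 : 1.6 over the visits with correlation 0.5. With the effect at week 12 only, the two AR(1) ratios are 0.40 and 0.435, and the growing-SD ratio is 0.05.

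**5. Adding a baseline covariate.** A participant's mean over the three rows is (b + y4 + y12)/3. Regress this on group and b. The b term in the mean is fully explained by the covariate and contributes zero to the group coefficient. What remains is (0 + a4 + a12)/3, where a4 and a12 are the baseline-adjusted differences. The factor 2/3 is unchanged.

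**6. Simulation check.** 300 trials, 25 per arm, 0.58 at both visits, change variance 2.505, assumed within-person correlation 0.5. Mean estimates:
- as written: 0.366 (expected 0.387; Monte Carlo standard error about 0.02)
- as written plus baseline covariate: 0.369
- group-by-time contrast at week 12: 0.538
- weeks 4 and 12 only, with baseline covariate: 0.553

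All four come from the same simulated data and run slightly low together. The telling figure is the ratio 0.369/0.553 = 0.667.

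**7. The interval.** With the baseline covariate, 22 per arm (44/2) and equal effects, the bias is 0.58/3 = 0.193. At correlation 0.5 the outcome variance is 2.51/(2 × 0.5) = 2.51. The baseline-adjusted variance of the two-visit mean is 2.51 × (0.75 − 0.25) = 1.255, so its standard error is √(1.255 × 2/22) = 0.338. The coefficient's standard error is 2/3 of that, 0.225. Bias over standard error is 0.86, so a nominal 95% interval covers 0.58 about 86% of the time. The same steps at correlations 0.3 and 0.7 give about 84% and 88%.

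**8. The test.** In step 5 the residual also scales by 2/3, so the estimate and its standard error shrink together. Simulated rejection rates were 0.39 for the written model with baseline covariate and 0.39 for the two-visit model with it. Without the covariate they were 0.22 for the written model and 0.21 for the week-12 contrast.

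**The case against.** The best defence is that the sentence begins by naming its target. With baseline as a time level, that target can only be the group-by-time contrast. A condensed article may list the factors and leave their interaction understood, and a separate analysis plan may spell it out. Part of this stands: the text nowhere says that an interaction is excluded, and one may well have been intended. It does not dispose of the point. The sentence enumerates its fixed effects, and the enumerated set cannot produce the stated target. That is a conflict within the text, not a detail deferred, and an analyst who follows the list reports a different number.

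Four stronger readings that a reader might draw are not supported:
- **That the plan rules out an interaction.** It only fails to list one.
- **That the effect is always cut by one third.** That figure needs a random intercept, complete data, and either equal effects at both follow-ups or the average post-baseline effect as target. The protocol fixes none of these.
- **That power is lost.** An apparent loss arises if the written model without a baseline covariate is set against an alternative with one. With the covariate in both, the rejection rate matches that of the averaged two-visit analysis.
- **That adjustment will be decided by looking at the data.** The clause on baseline imbalance allows that reading, but no test or threshold is given. It may simply mean that baseline is a covariate.

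**Conclusion.** The point holds as a mismatch between the stated target and the listed model, and it should be put right before analysis because it affects the primary outcome. Fitted literally, under a random intercept with complete data, the group coefficient has expectation 2/3 of the average post-baseline effect. Against the week-12 effect the shortfall is one third to two thirds over the trajectories examined; the other covariance structures tried give different figures, in some cases a much larger loss. A baseline covariate does not cure this while baseline remains a time level. The consequences are an estimate biased towards zero, an interval with less than nominal coverage, and no effect at either visit separately. If an interaction was intended all along, the defect is one missing phrase, but that phrase determines which number is reported.

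**What to change.** State that the estimate is the group-by-time contrast for PI-NRS at a named primary visit, with the other visit reported from the same model. Either form delivers it:
- model weeks 4 and 12 as outcomes, with group, time, group × time and the baseline value as covariate for all participants; or
- keep baseline as an outcome, for example with baseline means held equal across arms, and read the group-by-time contrast.

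Replace the clause on baseline imbalance with pre-specified baseline adjustment that applies whatever imbalance is observed. Use the same form for NDI and SF-12.

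Before the primary visit is named, the passages on timing must be reconciled: the outcome-collection section places the end of the intervention at week 4, while the intervention description runs it for 12 weeks.

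The cost is a few lines in the Statistical methods section. Baseline values are already collected, and no visit, measurement or participant is added.

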### Recruitment

To recruit participants for the trial, a comprehensive digital survey will be distributed to office workers to identify individuals experiencing NP from September 1 to October 30, 2025. The survey clearly explains the trial and its objectives and expresses that all information will be analyzed with strict respect to anonymity, confidentiality, and medical secrecy. By ticking a checkbox, individuals will express their voluntary commitment to join the study, and will have access to questions identifying general information (***e.g.,*** age, sex, comorbidities, work seniority, average number of daily hours spent in front of computer); the existence of NP, duration of symptoms, pain intensity, which will be evaluated via a pain intensity number rating scale (PI-NRS), medication (***e.g.,*** pain killers, physiotherapy). Individuals identified as potentially suffering from this condition will subsequently be invited to undergo a thorough physical examination by a specialist in the field (*SS* in the authors’ list) to confirm the diagnosis.

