### Eligibility criteria

Inclusion criteria will be the presence of a chronic NP lasting for more than three months, and a PI-NRS pain level at baseline assessment ≥ 3. Non-inclusion criteria will be acute NP, specific causes of NP (***e.g.,*** chronic inflammatory diseases), spine trauma or surgery, cervical radiculopathy or myelopathy, and physical therapy treatments in the last six months before baseline assessment.

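### The planned correlations with change scores carry no term for arm or baseline, so an outcome's own baseline, if included, would seem to predict improvement through measurement error alone

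*Protocol article*

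**What the plan says.** One sentence in Statistical methods covers this analysis: Spearman or Pearson coefficients "will be used to analyze the associations between clinical data and mean changes in the outcome measures". The threshold in the same paragraph is general: "Two-sided statistical significance is set at a p value < 0.05".

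The sentence does not mention arm, does not define clinical data, and does not say which baseline variables are meant. The phrase "and with adjustments for baseline imbalance" belongs to the preceding sentence, on the mixed model for the between-group comparison, and does not extend to the correlations.

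Baseline severity is collected more than once. The Recruitment survey asks for "duration of symptoms, pain intensity, which will be evaluated via a pain intensity number rating scale", alongside age, sex, comorbidities, seniority, computer hours and medication. Eligibility requires "a PI-NRS pain level at baseline assessment ≥ 3". The plans for outcome assessment have PI-NRS, NDI and SF-12 recorded at baseline by questionnaire. After randomisation, the trial also records adherence (Outcomes) and pain medication use (concomitant care).

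**The concern.** Change is baseline minus follow-up, so random error in the baseline reading enters both sides of a correlation between baseline and change. A worker who happens to score high at entry will tend to show a larger drop later, with no real link between severity and improvement. A bivariate coefficient cannot remove this.

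A second problem concerns variables recorded after randomisation. If adherence or medication use differs between arms and so does the change score, a pooled correlation picks up the arm difference even when the variable and the change are unrelated within each arm.

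At stake is a secondary result: a report that workers with worse pain improve more, when that may be only an artefact. The Discussion expects the findings to inform workplace wellness policy, so such a report could be given more weight than it deserves.

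**Working it through.** **The plan's figures.** The article states no number for the correlation analysis. Inputs from Sample size are the planned total of 50 (25 per arm), or 44 before the dropout allowance, and the earlier study's changes, which "were 2.23 ± 1.85 and 1.65 ± 1.26, respectively". From these, s² = (16 × 1.85² + 16 × 1.26²)/32 = 2.505 and d = 2.23 − 1.65 = 0.58, as the article has them. Reliability of PI-NRS, and its correlation between baseline and follow-up, are not given and are assumed below.

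**Step 1: an outcome's baseline against its own change.** Let baseline B and follow-up F have equal variance σ² and correlation r. If true improvement is the same for everyone, r equals the test-retest reliability. Then:

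- cov(B, B − F) = σ²(1 − r)
- var(B − F) = 2σ²(1 − r)
- corr(B, B − F) = (1 − r)/√(2(1 − r)) = √((1 − r)/2)

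The share of trials with p < 0.05 at n = 50 comes from simulation. It agrees with the Fisher approximation Φ(atanh(corr) × √47 − 1.96).

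| Assumed reliability | Correlation with improvement | Significant, simulated | Fisher approximation |
|---|---|---|---|
| 0.5 | 0.50 | 97% | 96% |
| 0.6 | 0.45 | 91–92% | 91% |
| 0.7 | 0.39 | 80–81% | 80% |
| 0.8 | 0.32 | 62–63% | 61% |

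The nominal rate is 5%. The entry cut at 3 narrows the baseline range and lowers these rates. With scores rounded to integers from 0 to 10, a simulation gave 94% down to 55% for reliability 0.5 to 0.8. With unrounded scores and an assumed mean of 5 and SD of 2, my check gave 87% and 43% at the two ends. The size depends on the assumed distribution, but the rate stays far above 5%.

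**Step 2: other baseline variables.** For a baseline variable unrelated to outcome, pooled over randomised arms with an arm effect of 0.58, the simulated rejection rate was 5.1% (n = 44) and 4.9% (n = 50). With an arm effect of 2.0 it was 5.2% at both sizes. There is no inflation.

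**Step 3: variables measured after randomisation.** Suppose the variable differs between arms by δ SD and is unrelated to change within arms. With equal arms pooled, corr = (δ × 0.58/4)/√((1 + δ²/4)(2.505 + 0.58²/4)).

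- δ = 0.5: 0.0725/√(1.0625 × 2.589) = 0.044
- δ = 1.0: 0.145/√(1.25 × 2.589) = 0.081
- δ = 1.5: 0.2175/√(1.5625 × 2.589) = 0.108

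Simulated rejection is about 5.5–6%, 8–9% and 11–12%. The inflation is real but modest.

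**Step 4: precision for ordinary baseline variables.** With equal variances and baseline-to-follow-up correlation ρ, the change score has variance 2σ²(1 − ρ). The follow-up score adjusted for baseline has residual variance σ²(1 − ρ²). The ratio is (1 + ρ)/2, which is 0.65 at ρ = 0.3 and 0.75 at ρ = 0.5. In a simulation of one real covariate effect, adjusting for baseline and arm raised power from 62% to 78% at ρ = 0.3 and from 76% to 85% at ρ = 0.5.

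**The case against.** The strongest reply is that the article commits to none of the harmful choices. It does not say that the arms are pooled, and it does not say that an outcome's baseline will be correlated with its own change. Most items in the Recruitment survey (age, sex, comorbidities, seniority, computer hours, symptom duration, medication) are not an outcome's baseline. The list of variables and the handling of arm are details that an article may leave to a fuller plan. The Objective sets no aim of finding predictors or effect modifiers.

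The survey pain score may also be a different reading from the baseline assessment used to compute change. With a separate survey reading as predictor, the simulated correlation with improvement is about 0.00 and rejection is about 5%. With the entry cut applied to the baseline assessment (assumed mean 5, SD 2), it is about −0.10 to −0.11, rejected in 10% to 12% of trials, and the sign is opposite to the coupling artefact.

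Most of this stands. A reader might infer that the analysis as planned pools the arms and will declare spurious predictors. The document does not support that. Pooling is not stated, it would not inflate false positives for baseline variables, and coupling does not touch age, sex, seniority, hours or symptom duration.

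One part of the reply does not hold. The choice of method is stated, so it is not a missing detail. The sentence names a coefficient that can adjust for neither arm nor baseline, and nothing in the text keeps the baseline PI-NRS, NDI or SF-12 out of it.

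**Conclusion.** The concern holds conditionally and is of modest priority. The protocol fixes an unadjusted method that would produce an artefact if an outcome's baseline assessment score is among the clinical data: r of about 0.50 to 0.32, significant in about 97% to 62% of trials with no true association. This rests on n = 50, equal variances at both times, equal true improvement for all, and assumed reliability of 0.5 to 0.8. The entry cut lowers the rates without removing the problem.

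For variables recorded after randomisation, pooling the arms would raise the false-positive rate to about 5.5% to 12% for arm differences of 0.5 to 1.5 SD, also an assumed range. For other baseline variables the cost is lost precision and not bias.

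The between-group comparison is a separate model, so neither it nor the sample size is affected.

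**What to change.** Replace the correlation sentence with a regression or mixed model of the follow-up score on arm, that outcome's baseline score and the clinical variable, for PI-NRS, NDI and SF-12. State that an outcome's baseline will not be correlated with its own change. Report coefficients with 95% confidence intervals and label the analysis exploratory. For adherence and medication use, add that even an arm-adjusted association is not causal, because these are measured after randomisation.

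Arm-by-variable interactions are optional. They would be imprecise with 25 per arm and are needed only if the question is who benefits from the app.

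The cost is a sentence or two of text and a few lines of SPSS syntax, with no new data. The downside is slightly more analysis work and fewer nominally significant associations to report.
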